#### Sham-taVNS group

Participants in Sham-taVNS group will receive Sham-taVNS and usual care. The points, stimulator and stimulating parameters used in Sham-taVNS group are the same with taVNS group. However, we cut the inner electric wire of the stimulator to prevent the current output. Usual Care: the same with the taVNS group.

**Fig. 2 Fig2:**
[figure not shown]
Study periods FPVCs: Frequent premature ventricular complexes; R: Randomization; taVNS: transcutaneous auricular vagus nerve stimulation

**Fig. 3 Fig3:**
[figure not shown]
Auricular points stimulation of taVNS and sham-taVNS groups HX1: auricular point of Erzhong; CO15: auricular point of Xin; taVNS: transcutaneous auricular vagus nerve stimulation

### Outcome

The primary outcome is the proportion of participants with a ≥ 50% decrease of PVCs from baseline at the end of week 6. The PVCs will be assessed by a 24-h Holter. We will calculate the decrease of PVCs between baseline and week 6 (at the end of the treatment) and obtain the proportion of patients with a decrease of 50%.

Secondary outcomes include: (1) the proportion of participants with a ≥ 50% decrease of PVCs from baseline at the end of week 18 and the proportion of participants with a ≥ 75% decrease of PVCs from baseline at the end of week 6 and 18 which will be assessed the same way as the primary outcome; (2) the change from baseline in PVCs, total cardiac impulse and supraventricular premature contractions at the end of week 6 and 18 which will also be assessed through a 24-h Holter; (3) the score change from baseline in the symptom of palpitation, chest tightness, dizziness or insomnia at the end of week 6 and 18; the change of the proportion of participants with moderate/severe symptoms of palpitation, chest tightness, dizziness or insomnia from baseline at the end of week 6 and 18; The symptom of palpitation will be assessed by a 10-scale VAS from 0 to 10, a higher score indicates a more severe symptom; Score 4–6 are defined as the moderate level, Score 7–10 are defined as the severe level; (4) the score change from baseline in the Self Anxiety Scale (SAS) at the end of week 6 and 18. SAS contains 20 items scoring from 25 to 100. The higher the score significates the greater anxiety. (5) the score changes from baseline in the Self Depression Scale (SDS) at the end of week 6 and 18. SDS contains 20 items scoring from 25 to 100. The higher the score significates the greater depression. (6) the score changes from baseline in 36-Item Short Form Health Survey (SF-36) at the end of week 6 and 18. The SF-36 questionnaire contains eight scales with two measures: physical and mental health. The physical health includes four scales of physical functioning, role-physical, bodily pain, and general health. The mental health is composed of vitality, social functioning, role emotional, and mental health. SF-36 scores from 0 to 100, higher scores indicate better health status.7) subgroup analysis of ages (classified as ≤ 40 years and > 40 years), sex and the severity of PVCs (classified as Grade 2, 3, and 4 A according to Lown grading system) on the primary outcome. 8) the proportion of participants with treatment-related adverse events between two groups.

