**Methods:**

The study is a prospective, randomized, parallel-controlled trial with a 1:1 ratio between the two groups. Patients will be randomized to either the treatment group (taVNS) or the control group (Sham-taVNS) with a 6-week treatment and a subsequent 12-week follow-up period. The primary outcome is the proportion of patients with a ≥ 50% reduction in the number of PVCs monitored by 24-hour Holter. Secondary outcomes include the proportion of patients with a ≥ 75% reduction in PVCs, as well as the changes in premature ventricular beats, total heartbeats, and supraventricular premature beats recorded by 24-hour Holter. Additional assessments compared score changes in PVCs-related symptoms, as well as the score change of self-rating anxiety scale (SAS), self-rating depression scale (SDS), and 36-item short form health survey (SF-36).

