**Discussion:**

The TASC-V trial will help to reveal the efficacy and safety of taVNS for frequent PVCs, offering new clinical evidence for the clinical practice.

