Transcutaneous auricular vagus nerve stimulation (taVNS) is a non-invasive and safe physical therapy, which could stabilize the heart rhythm by stimulating the vagus nerve [15]. The vagus nervous system belongs to the autonomic nervous system, and the heart is regulated by the autonomic nervous system. Dysregulation of the autonomic nervous system, such as decreased vagal activity and increased sympathetic activity, can lead to arrhythmias and more serious cardiovascular diseases [16]. The autonomic nervous system can be regulated by taVNS, which could further enhance the excitability of the vagus nerve, inhibit the activity of the sympathetic nerve, and bring the autonomic nervous system to a balanced state [16]. In addition, taVNS has been shown to reduce ventricular interstitial fibrosis, reduce the possibility of ventricular arrhythmias, and stabilize the electrophysiological conduction of cardiomyocytes in models of heart diseases such as myocardial infarction and heart failure [17]. The auricular point CO15 (Xin) is in the concha cavity, and HX1 (Erzhong) is in the middle point of the helix, both are in the area of auricular vagus nerve distribution [18]. Stimulating on these two points can modulates the excitability of the vagus nerve [19]. Besides, laboratory studies have shown that needling in PC6 (Neiguan) and HT7 (Shenmen) stabilizes heart rate by blocking ion channels in tachyarrhythmia cardiomyocytes and stimulating parasympathetic nerves [20–22].

Although there was clinical and experimental basis of taVNS for PVCs, but the high-quality clinical studies are limited with insufficient evidence of efficacy. This study preliminarily evaluated the efficacy of taVNS in reducing the number of PVCs in patients with frequent PVCs, and evaluated the acceptability and safety of patients, laying a foundation for further clinical research.

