**Fig. 1 Fig1:**
[figure not shown]
Flowchart of Study PVCs: premature ventricular complexes; taVNS: Transcutaneous auricular vagus nerve stimulation

**Table 1 Tab1:** Study schedule by time

Period	Baseline	Treatment						Follow-up		
**Week**	**-1**	**1**	**2**	**3**	**4**	**5**	**6**	**10**	**14**	**18**
Screening	**×**									
Informed consent	**×**									
Demographic data	**×**									
Eligibility	**×**									
Factors that affect heart rate	**×**	**×**	**×**	**×**	**×**	**×**	**×**	**×**	**×**	**×**
History of present illness	**×**									
Previous treatment history	**×**									
Vital signs	**×**	**×**	**×**	**×**	**×**	**×**	**×**	**×**	**×**	**×**
Complete blood analysis	**×**									
Cardiac B ultrasound	**×**									
24-hour Holter	**×**						**×**			**×**
Total cardiac impulse by 24-h Holter	**×**						**×**			**×**
Premature ventricular contractions by 24-h Holter	**×**						**×**			**×**
Supraventricular premature contractions by 24-h Holter	**×**						**×**			**×**
Combined treatment/medication	**×**	**×**	**×**	**×**	**×**	**×**	**×**	**×**	**×**	**×**
VAS for PVC-related symptoms	**×**	**×**	**×**	**×**	**×**	**×**	**×**	**×**	**×**	**×**
Self-rating anxiety scale (SAS)	**×**						**×**			**×**
Self-rating depression scale (SDS)	**×**						**×**			**×**
The short form health survey (SF-36)	**×**						**×**			**×**
Evaluation of treatment associated adverse events		**×**	**×**	**×**	**×**	**×**	**×**			
Evaluation of adherence							**×**			
Evaluation of acceptability							**×**			

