### Blinding

Acupuncturists could not be blinded for that the taVNS is a manipulating intervention. The participants, outcome evaluator and statistician are blinded. Patients will accept taVNS in the treatment group, and sham-taVNS without any current output in the controlled group. For the blinding, patients in both groups were told that the feelings of stimulation they would receive might vary individually, with some could feel it and others could not feel it at all. During the treatment, the sound of adjusting the current was the same in both groups.

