The regulation of the cardiac function is significantly influenced by the vital role played by the vagus nerve. From the anatomical structure, the postganglionic efferent vagus nerve is distributed throughout most of the cardiac system including the atria, the sinoatrial node, the atrioventricular node, the ventricles, et al. [12]. Stimulation of the vagus nerve can reduce the cardiac rate, atrioventricular conduction and ventricular contractility [25]. Clinical studies have revealed that vagus nerve stimulating can relieve the atrial fibrillation and heart failure by improving the heart rate variability and the left ventricular ejection fraction [26–28], which is also supported by animal research [29–31]. Although not as much as the research on atrial fibrillation and heart failure, there are also some animal studies focusing on the mechanism of vagus nerve stimulation for the ventricular arrhythmia. Vagus nerve stimulation could inhibit the enhancement of sympathetic nerve activity by ventricular muscle [32] and reverse the ventricular arrhythmias induced by high sympathetic nerve stimulation, especially inhibit the ventricular fibrillation and stabilize the ventricular electrophysiological changes [33]. However, this protective effect on the ventricle can also be affected by some drugs, such as atropine and β-blockers [34]. Besides, the vagus nerve was able to regulate the NO release, which could contract blood vessels, by the ventricular myocytes in order to improve the myocardial systolic and diastolic function, increase coronary blood flow, and improve cardiac function [35]. In terms of ventricular electrophysiology, vagus nerve could reduce the maximum slope of the electrocardiogram recovery curve and increase the effective refractory period in the excitatory cycle of ventricular myocytes [36]. Due to the risk and complexity of ventricular arrhythmias, there are relatively few clinical studies. For the vagus nerve stimulation for PVCs, especially the taVNS for PVCs, we only searched out a study protocol, which was registered in 2021, later than our registration.

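### Adverse events are compared by arm only if judged treatment-related, and are scheduled for evaluation only in weeks 1-6 of 18, which weakens the promised safety conclusion

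*Protocol article*

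**What the plan says.** In the protocol article, Outcome section, the eighth secondary outcome is "the proportion of participants with treatment-related adverse events between two groups". It is the only adverse-event outcome listed, and its sentence gives no time window.

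The schedule (Table 1) has a single adverse-event row, "Evaluation of treatment associated adverse events". It is marked at weeks 1, 2, 3, 4, 5 and 6 and left empty at weeks 10, 14 and 18. At those three later visits the same table does mark vital signs, the symptom scale, combined treatment and factors affecting heart rate. Holter, the anxiety and depression scales and SF-36 are marked at week 18.

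The Abstract describes a "6-week treatment and a subsequent 12-week follow-up period". Safety is a stated aim in the Background ("evaluated the acceptability and safety of patients") and a promised conclusion in the Abstract ("The TASC-V trial will help to reveal the efficacy and safety of taVNS for frequent PVCs"), repeated in the Conclusion.

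The Blinding section says "The participants, outcome evaluator and statistician are blinded", and that the acupuncturists are not blinded. No section says who decides whether an event is related to treatment.

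**The concern.** With a sham arm that receives no current, and with blinded participants and evaluator, the design can show whether events are more frequent under active stimulation simply by counting them in each arm. No causal opinion on any single event is needed. The eighth secondary outcome applies such an opinion first and compares what is left.

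Two things can then go wrong.

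- If the same share of events is called related in both arms, any true excess is reported too small unless that share is 100%.
- If the share differs between arms, which is possible if anyone aware of allocation contributes to the judgement, a difference can be created or hidden.

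The document itself gives a reason for care. Its Discussion states that "Stimulation of the vagus nerve can reduce the cardiac rate, atrioventricular conduction and ventricular contractility". A slow heart rate or dizziness in a patient with frequent PVCs, who may be on permitted medication, is easily put down to the disease or the drug.

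The schedule adds a second restriction: an adverse event in weeks 7 to 18 has no planned point of evaluation. At stake is the safety conclusion. The primary efficacy analysis is not affected.

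**Working it through.** The article gives no adverse-event rate and no precision statement for safety, so there is no figure of the plan's own to reproduce. The coverage figures come from Table 1 and the 45 participants per arm from the Sample size calculation section. All risks, attribution shares and background rates below are assumptions for illustration.

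**1. Coverage.** Post-baseline visits are weeks 1-6, 10, 14 and 18, which is 9. The adverse-event row is marked at 6 of them. Weeks without evaluation: (18 − 6)/18 = 12/18 = 67%.

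**2. Same share called related in both arms.** Assume treatment-caused or equivalent events in 15% (taVNS) and 2% (sham), and that unrelated background events are never called related. Reported difference = share × (15% − 2%). Power is for an exact two-sided Fisher test at 0.05 with 45 per arm.

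| Share called related | Reported risks | Difference (points) | Power |
|---|---|---|---|
| 25% | 3.75% vs 0.5% | 3.3 | 0.5% |
| 50% | 7.5% vs 1.0% | 6.5 | 8% |
| 75% | 11.25% vs 1.5% | 9.8 | 25% |
| 100% | 15% vs 2% | 13.0 | 45% |

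**3. Counting all events.** With an independent background risk b in both arms, risk = 1 − (1 − r)(1 − b), where r is 15% or 2%.

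| b | Risks | Difference (points) | Power |
|---|---|---|---|
| 10% | 23.5% vs 11.8% | 11.7 | 22% |
| 20% | 32.0% vs 21.6% | 10.4 | 14% |
| 30% | 40.5% vs 31.4% | 9.1 | 11% |

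These differences do not move with attribution, but background events dilute them.

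**4. Different shares by arm.** Assume the all-event risk is 20% in both arms, so there is no true difference. With 60% vs 30% called related, the outcome reads 0.20 × 0.60 = 12% vs 0.20 × 0.30 = 6%, a false difference of 6 points. With 80% vs 20% it reads 16% vs 4%, a false difference of 12 points. The all-event count would show 20% in each arm.

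**5. Precision either way.** With no events among 45 participants, the exact upper limit of the two-sided 95% interval is 1 − 0.025^(1/45) = 7.9%. Any adverse-event comparison of this size is descriptive.

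**The case against.** A reader might infer that the safety conclusion rests on a relatedness judgement in place of the randomised comparison. The text does not support that: the outcome is still compared between the two randomised groups, only on a filtered set of events.

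A reader might also infer that nothing about safety is collected after week 6. That is not so either. Secondary outcomes 2 to 6 compare PVCs, supraventricular beats, total heartbeats, symptom scores, the anxiety and depression scales and SF-36 at weeks 6 and 18, none of them dependent on attribution. The third also includes "the change of the proportion of participants with moderate/severe symptoms of palpitation, chest tightness, dizziness or insomnia". Total heartbeats over 24 hours is in effect mean heart rate. The 67% figure therefore describes one row of the schedule. What remains is that these outcomes are group summaries and do not cover other kinds of adverse event.

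Nor do the calculations show that counting all events is statistically stronger. If attribution is good, the related-only count does as well or better: power is 45% or 25% when 100% or 75% of events are called related, against 22%, 14% or 11% for all events. At 50% or 25% called related it does worse, at 8% or 0.5%. The document gives no basis for choosing among these.

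The article is a condensed protocol, and the full protocol or case report form may say how other events are captured and who judges them. It would be wrong to claim that unrelated events go unrecorded. But the restriction here is stated, in the outcome and again in the schedule. An analysis plan can retabulate recorded events; it cannot recover events that were not asked about.

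Finally, evaluating adverse events only during treatment is a common choice for a non-invasive intervention that stops at week 6, and most stimulation effects would probably appear then. The attribution filter is therefore the more important half of the point.

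**Conclusion.** The point holds, at minor to moderate severity. As written, the only adverse-event outcome and the only adverse-event row are restricted to events judged related, with evaluation at 6 of 9 post-baseline visits and none scheduled in the last 12 of 18 weeks. The comparison by arm is randomised but depends on a judgement whose assessor is not named, in a trial where the treating staff know the allocation. This weakens a safety conclusion that the article promises.

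The coverage figures are read directly from Table 1. The size of any distortion is not known: the range of 3.3 to 13.0 points for a true 13.0, and the false differences of 6 or 12 points, rest wholly on assumed risks and shares. The case for change is less exposure to judgement. No gain in power is claimed, and no primary result or error rate is affected.

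**What to change.** Reword the eighth secondary outcome and the Table 1 row so that all adverse events are recorded regardless of attribution, and mark the row at weeks 10, 14 and 18 as well. Report the number and proportion of participants with any adverse event by arm, descriptively. Keep treatment-related events as a subset, classified by the blinded outcome evaluator.

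The Study design section gives a start in June 2020 and an anticipated end in June 2024, so many participants may already have been treated. For them, report by arm every event that was recorded, and state that related-only collection in weeks 1-6 limits the safety conclusion.

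The cost is a wording change in two places, an adverse-event question at three visits that already take place, and slightly more tabulation. No new visit or procedure is needed. The downside is that background events will dilute the difference between arms.

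Optionally, and not as part of this correction, the stored data could also give descriptive counts by arm of participants with blood pressure at or below the entry limit of 90/60 mmHg, and of bradycardia or second-degree or higher atrioventricular block on the week 6 Holter. The latter needs an extra read and a bradycardia threshold fixed before unblinding.

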### Sample size calculation

The null hypothesis is that there would be no difference between the two groups in the proportion of participants with a ≥ 50% reduction of PVCs from baseline after 6 weeks of treatment, and the alternative hypothesis is that there would be a significant difference between the two groups. In our pilot study, the proportion in taVNS and sham-taVNS groups were 58.3% and 21.1%, separately. Ninety participants are required (45 in each group) with a two-tailed test setting power as 90% and alpha as 5%, and considering the rate of loss to follow-up as 15%. To balance the three sites with two groups, 30 participants need to be enrolled in each site (15 per group in one site).

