### Statistical analysis

All analyses will be performed using the intention-to-treat population and a *p* value of 0.05 will be taken to indicate a statistically significant effect. The primary analysis will seek to demonstrate the ratio difference of participants with a ≥ 50% decrease of PVCs from baseline at the end of week 6 between taVNS and sham taVNS groups. We will use a generalized linear mixed model to estimate the differences from baseline and between groups. The random effect for participants will be included, the fixed effects include 1 with-subject variable (time point) and 1 between-subject variable (group). Other secondary outcomes with the same pattern of longitudinal data will be analyzed use the similar way as primary analysis. The intervention effect will be summarized as the ratio difference and its 95% confidence interval. For continuous process indicators such as Holter related outcomes and patient reported outcome measures (SAS, SDS, SF-36), we will use mixed effect linear model. A detailed analysis plan including mock tables will be completed before unblinding. For missing data of primary outcome, the multiple imputation method will be used under the missing-at random assumption to generate 100 imputed data sets. All analyses and summaries will be performed by using SAS version 9.4.

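### The plan balances the arms within each of three sites, but the stated primary model has neither site nor baseline PVC count; the cost is some precision, not validity

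*Protocol article*

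**What the plan says.** All references are to the protocol article.

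- **Sample size calculation.** The total is split evenly over three sites and two arms: "30 participants need to be enrolled in each site (15 per group in one site". The stated purpose is balance of arms across sites.
- **Randomization.** The list was generated with SAS PROC PLAN and put in numbered opaque envelopes. Neither strata nor blocks are mentioned.
- **Statistical analysis, primary outcome.** A generalized linear mixed model is used, with a random effect for participant; "the fixed effects include 1 with-subject variable (time point) and 1 between-subject variable (group". The effect is reported as a difference in proportions with a 95% confidence interval.
- **Statistical analysis, continuous outcomes.** A linear mixed model is named, without a list of its terms. A detailed analysis plan is promised before unblinding.
- **Outcome and Table 1.** Holter counts, symptom VAS, SAS, SDS and SF-36 are collected at baseline. The continuous outcomes are defined as changes, for example "the change from baseline in PVCs, total cardiac impulse and supraventricular premature contractions at the end of week 6 and 18".

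**The concern.** When allocation is forced to balance within site, the two arms cannot differ by chance in their mix of sites. An analysis that ignores site still counts between-site variation as noise in the treatment difference. Its standard error is then larger than the true sampling variation, the interval is too wide and the test rejects too rarely.

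Baseline PVC count enters the primary outcome only through the definition of response. Response has no value at baseline, so baseline cannot enter that model as a time level either.

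The article is not silent here. It counts the between-subject variables as one and names it as group. An analysis plan that follows this wording leaves out site and baseline, and one that adds them departs from the published model. What is at stake is precision in a trial of 90 that describes its own sample as small.

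**Working it through.** **Inputs from the article.** Response rates: "the proportion in taVNS and sham-taVNS groups were 58.3% and 21.1%, separately". Error rates: "with a two-tailed test setting power as 90% and alpha as 5" percent. Dropout: "considering the rate of loss to follow-up as 15" percent. Size: "Ninety participants are required (45 in each group". Design: "parallel-controlled trial with a 1:1 ratio between the two groups". There are three sites with 15 per arm in each. The article gives no between-site difference and no baseline to follow-up correlation, so ranges are assumed for both.

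**1. The plan's own figure.** The pooled two-proportion formula gives n0 = 34.23 per arm, with d = 0.583 − 0.211 = 0.372. The continuity correction gives (34.23/4) × [1 + √(1 + 4/(34.23 × 0.372))]² = 39.42. Inflated by 1.15 this is 45.33 per arm, in line with the stated 45 per arm and 90 in total. Nothing below changes this figure.

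**2. Is restriction within site implied?** Simple randomisation of 30 per site gives 15/15 in all three sites with probability (C(30,15)/2³⁰)³ = 0.3%. A single list fixed at 45/45 overall, ignoring site, gives it with probability C(30,15)³/C(90,45), about 3.6%. As a target, 15 per arm per site is realistic only with allocation controlled within site. This is an inference, not a statement in the article.

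**3. Closed-form size.** The variance sum without site is 0.583 × 0.417 + 0.211 × 0.789 = 0.4096. If site response rates are shifted by −e, 0 and +e in both arms, the within-site sum is 0.4096 − 4e²/3.

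- e = 0.15: 0.3796; SE ratio √(0.4096/0.3796) = 1.04; 1 − 0.3796/0.4096 = 7% of the sample.
- e = 0.20: 0.3563; SE ratio 1.07; 13% of the sample.

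**4. Simulation.** There were 200,000 simulated trials per setting, with 15 per arm per site and site effects as logit shifts of −d, 0 and +d. Overall rates were held at the planning values. An unstratified two-proportion test and SE were compared with the Cochran–Mantel–Haenszel test and a site-stratified SE. Type I error was taken at null rates of 21.1% and 40%. The mixed model itself was not fitted.

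| d | Sham rate by site, % | SE unstratified | SE stratified | Ratio | Type I unstratified, % | Type I stratified, % | Power unstratified, % | Power stratified, % |
|---|---|---|---|---|---|---|---|---|
| 0 | 21.1 in all | 0.0942 | 0.0953 | 0.99 | 4.9–5.5 | 4.7–5.0 | 96.1 | 95.9 |
| 0.5 | 13.4, 20.3, 29.6 | 0.0943 | 0.0936 | 1.01 | 4.5–5.1 | 5.0 | 96.4 | 96.7 |
| 1.0 | 7.5, 18.1, 37.6 | 0.0944 | 0.0894 | 1.06 | 3.5–4.4 | 5.0–5.2 | 97.0 | 97.9 |
| 1.5 | 3.8, 15.1, 44.4 | 0.0945 | 0.0837 | 1.13 | 2.2–3.5 | 4.9–5.0 | 97.7 | 98.9 |

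The 5.5% at d = 0 occurs with no site effect at all, so it is not due to omitting site. With 13 per arm per site after dropout (15 × 0.85 = 12.75), power is 94.7% against 95.8% at d = 1.0, and 95.7% against 97.7% at d = 1.5.

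**5. Continuous outcomes.** Assume equal variance at baseline and follow-up, and correlation r. An unadjusted change score has variance factor 2(1 − r); baseline as a covariate gives 1 − r². The ratio is (1 + r)/2: 65%, 75%, 85% and 90% at r = 0.3, 0.5, 0.7 and 0.8.

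**The case against.** **The error is on the safe side.** Leaving out a factor used to balance allocation makes the analysis conservative. A reader might infer that the standard errors are invalid or that false positives increase; the calculations show the opposite. This objection stands and limits the weight of the point.

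**The size is assumed.** The article gives no site effect. With no difference between sites there is no gain, and the stratified SE is even slightly larger (0.0953 against 0.0942). A shift of 20 points around a sham rate of 21.1% would put one site near 1% and another near 41%, which is a large spread. This stands, so the low end of the range has to be shown with the high end.

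**Stratification is not stated.** The site numbers are an enrolment target, and the Randomization section names no strata. This stands. If allocation was not in fact restricted by site, the unadjusted SE would suit its design, and adjustment would only gain precision.

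**The continuous outcomes may already be handled.** A reader might infer that they are to be analysed as unadjusted change scores. The article does not say so. A change from baseline defines the outcome, not the estimator; the list of fixed effects is given for the primary model; and baseline may be a time level in the linear mixed model. If baseline means are constrained equal between arms, that model gains about as much as covariate adjustment. If they are free, then with complete data it reproduces the change-score comparison. The article leaves this open.

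**The value of baseline PVC count for the primary outcome is not shown.** Nothing in the article says how well it predicts a relative reduction of at least 50%, so no size is claimed for it.

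**The detail could be left to the analysis plan.** For the continuous outcomes this is fair. For the primary outcome it is not, because the article states the terms and allows one between-subject variable.

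**Conclusion.** The point holds as a matter of efficiency. The primary model, as listed, leaves out the factor on which allocation is evidently meant to be balanced, and a baseline count the trial already collects. There is no bias in the difference in proportions and no inflation of the type I error.

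Over logit shifts of 0.5 to 1.5, the standard error is about 1% to 13% too large. Power on the primary outcome falls by 0.3 to about 2 points from a level already above 90%; with no site difference, nothing is lost. These figures rest on assumed site effects, on allocation actually restricted by site, and on simple stratified and unstratified comparisons in place of the mixed model.

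For the continuous outcomes the potential gain is larger, with variance reduced to between 65% and 90%. It applies only if the alternative is an unadjusted change score or a model with unconstrained baseline means, and it depends on the assumed correlation. The stronger conclusion that the plan commits to unadjusted change scores is not supported by the article.

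**What to change.** Before unblinding:

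1. **Primary outcome.** Add site (three levels) and log baseline 24-hour PVC count as pre-specified covariates. Standardise the fitted model back to the planned difference in proportions with its 95% confidence interval, so that the reported effect measure does not change.
2. **Continuous outcomes.** List the model terms. Add site, and either use the baseline value of the outcome as a covariate or constrain baseline means to be equal between arms.
3. **Randomization section.** State whether allocation was restricted within site, and how, so that it agrees with the Sample size section.

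The cost is wording. The sample size stays at 90, and no procedure or data collection changes. About 36 responders are expected (45 × 0.583 + 45 × 0.211 = 35.7), fewer among those observed after dropout. Group, two site terms and one baseline term make four parameters; the time terms come on top, so the covariate list should stay this short. The covariates must be fixed before unblinding, because if added later they could appear to have been chosen by result.
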